**Figure 3 figure3:**
[figure not shown]
Sample posts from the private, in-app Pink Body Spirit Fitbit Community (note: app screenshots have been redacted to maintain confidentiality).

#### Toolbox

Peer mentors will be encouraged to individualize the intervention through the use of a *toolbox* of exercise-related strategies and materials to help participants overcome barriers and achieve their unique exercise goals. Peer mentors will be able to spend up to US $40 on each participant to provide them with toolbox items such as fitness apps (free or paid), exercise materials for home-based workouts (eg, resistance bands, stability ball, or jump rope), and information about free workouts or exercise groups. Peer mentors can offer toolbox resources any time after the first session, and they must be linked with the participant’s individual exercise goal and action plan. Development of the toolbox was guided by the Haus of Volta Community Advisory Board’s field testing. The flexible, individualized toolbox approach has been a key component of numerous successful lifestyle interventions [57,58].

### Postintervention Follow-Up Period (Months 4 to 6)

The postintervention follow-up period in months 4 to 6 will focus on exploring the extent to which participants continue to engage with their mentors and different aspects of the Pink Body Spirit program beyond the initial 3-month intervention. There will be no scheduled contacts or video chat sessions with peer mentors during the follow-up period, but participants will still be encouraged to continue wearing and syncing their Fitbit to track their activity and participate in the Pink Body Spirit Fitbit Community. Peer mentors will be advised that they are not expected to check activity data on Fitabase once a mentee has entered the follow-up period. Although there are no planned sessions, some contacts may still occur. If a peer mentor chooses to communicate with a mentee during the follow-up period, it will be tracked in the REDCap database (date of support, mode [eg, email, Fitbit message, text, call, or Zoom video chat], and general reason for support).

### Measurement

#### Baseline Assessment (T0)

Participants will be emailed a link to a battery of web-based questionnaires consisting of quality of life measures, theoretical constructs for physical activity change, and self-reported muscle strengthening, stretching, and flexibility exercises. Participants will self-report demographics, general medical history, menstrual and reproductive history, and cancer history. Self-reported general medical history will include all current conditions and medications prescribed by a health care provider and dietary and nutritional supplements. Self-reported menstrual and reproductive history will include any history of hysterectomy and/or oopherectomy, age at first menstrual period, last menstrual period, and/or reason(s) period has stopped. Self-reported cancer history will include date of diagnosis, stage at diagnosis, type of surgery, date of surgery, cancer treatments (radiation, chemotherapy, and/or hormonal therapy, history and current), infusions for human epidermal growth factor receptor 2-positive breast cancer (eg, Herceptin, history and current), and lymphedema (history and current).

Once the questionnaires have been completed, participants will be mailed an ActiGraph GT3X+ accelerometer, a device that objectively measures activity, and instructed to wear it on the hip for the next 7 days during waking hours (for at least 12 hours per day). Two compliance reminders will be placed over the 7-day wear period. Once the ActiGraph has been worn for 7 days for at least 12 hours per day, participants will return it to the study office using a prepaid envelope. Upon receipt, ActiGraph data will be screened for sufficient wear time. If participants have not worn the device for at least 10 hours over 5 days or 50 hours over 4 days, they will be mailed another device and asked to rewear it. Participants will receive US $20 for completing the T0 measures. All T0 measures will be completed, and sufficient wear time will be verified before being matched with a peer mentor to begin the exercise program.

#### Postintervention Assessment (T1)

Three months after completing the first intervention session with their peer mentor, participants will repeat the web-based questionnaires completed at T0 and complete a 3-month quantitative satisfaction questionnaire. They will again be mailed an ActiGraph and asked to wear it for 7 days. The same wear and mail-back instructions and compliance protocol described above will be used. After returning the ActiGraph, participants will complete a 3-month qualitative interview. Participants will receive US $20 for completing the ActiGraph and questionnaire and US $10 for the individual interview.

#### Follow-Up Assessment (T2)

Six months after completing the first intervention session with their peer mentor, participants will repeat the web-based questionnaires completed at T0 and complete a 6-month quantitative satisfaction questionnaire. They will again be mailed an ActiGraph and asked to wear it for 7 days. The same wear and mail-back instructions and compliance protocol described above will be used. After returning the ActiGraph, participants will complete a 6-month qualitative interview. Participants will receive US $20 for completing the ActiGraph and questionnaire and US $10 for the individual interview.

### Measures and Outcomes

#### Feasibility and Acceptability

##### Recruitment and Retention

We will report recruitment and retention using a Consolidated Standards of Reporting Trials diagram. We will track those who contact the study office via phone or email. Specifically, we will track the number of women who contact the study office, referral source for each (eg, social media, community event, UC San Diego patient navigator), number of women phone screened, number of eligible participants, and number of participants enrolled in the study. We will compare the yield from different recruitment approaches and assess if any eligibility criteria have excluded a disproportionate number of otherwise eligible women.

##### Adherence

Adherence to the intervention will utilize several metrics: completion of intervention sessions, wearing the Fitbit, and posting in the Fitbit Community. Adherent will be defined as completing 2 out of 3 of the following activities: completing >75% of the sessions, wearing the Fitbit on >75% of the days, or posting in the Fitbit Community at least once per week for >75% of the weeks.

#### Mixed Methods Evaluation

A parallel mixed methods approach will be used to explore the feasibility, acceptability, and satisfaction of the Pink Body Spirit intervention from the participants’ perspectives. Quantitative satisfaction questionnaires will be used to gain breadth of understanding, and qualitative interviews will add depth of understanding [59].

##### Quantitative Satisfaction Questionnaire (Postintervention and Follow-Up)

Questionnaires will build off questions used to evaluate the previous intervention in older breast cancer survivors upon which the Pink Body Spirit program is based [41]. Topics will include overall ratings of the program, the extent to which the program provided motivation to start and continue exercising, and the likelihood of recommending the program to other younger survivors. A series of items using Likert-scale response options will assess self-reported frequency of use, satisfaction with, and helpfulness of each intervention component. Participants will be asked to rate different features of the Fitbit tracker, the Fitbit app, and the Fitbit Community. There will be a *did not use* option for each feature assessed. Participants will also be asked to rate their satisfaction with the number, length, and content of peer mentoring sessions as well as the Zoom video conferencing format. Open-ended questions will ask participants to describe their favorite and least favorite aspects of the program and provide suggestions for how to improve Pink Body Spirit. Additional topics for the T2 questionnaire will include continued use of intervention components, including the Fitbit, Fitbit Community, and toolbox items, after the 3-month intervention has formally concluded; the extent to which participants continue to communicate with peer mentors; and participants’ interest in being trained to serve as a peer mentor in a future study or program. To assess general attitudes toward Pink Body Spirit, we will use items from 2 validated, Likert-type measures of feasibility and acceptability [60]. Questionnaires will be piloted internally with the research and peer mentor teams before use.

##### Qualitative Interviews

At T1 and T2, individual, semistructured interviews will be conducted via Zoom video conferencing. Each interview will last approximately 45 min. Interviews will be video recorded and uploaded to the UC San Diego server. Interviews will explore topics such as overall perceptions of the intervention and specific components (eg, peer mentors and Fitbit), barriers and facilitators to behavior change, perceived health benefits (particularly in the targeted domains of body image, sexual functioning, and fatigue), the remote delivery format, and ways to improve the Pink Body Spirit program for other young breast cancer survivors. Semistructured interviews are proposed to keep the interview prioritized and targeted, but also allow for the flexibility to use additional probes to clarify responses and add depth to participants’ answers. Interview questions will be asked in a flexible order, and wording may be adapted to maximize each participant’s understanding. The interview guide will be piloted internally with the research team and with younger breast cancer survivors not involved in the study before administration. For consistency, [name] will conduct all interviews with the participants.

#### Physical Activity

##### ActiGraph GT3X+

The ActiGraph GT3X+ (ActiGraph, LLC) will be used to measure changes in minutes of MVPA from T0 to T1 and T1 to T2. This is the gold standard measure of free-living physical activity that provides blinded data collection. For 7 days around each measurement time point, participants will wear the ActiGraph GT3X+, a research grade, hip-worn accelerometer that measures movement and intensity of activity and that has been validated against heart rate telemetry and total energy expenditure. Physical activity data are not shown to the wearer. The GT3X+ provides second-by-second estimates of activity that can be categorized into minutes spent in sedentary, light, moderate, and vigorous activity using calibration thresholds. Sufficient wear time will be defined as 5 days with ≥600 min of wear time or 3000 min (50 hours) across 4 days. Time spent in sedentary behavior and light, moderate, and vigorous activity will be derived using Freedson cut-points [61].

##### Fitbit Charge 3

Data from the Fitbit Charge 3 will be used to calculate daily adherence to wearing the Fitbit throughout the intervention and to support peer mentoring. Participants will be asked to wear the Fitbit for as many hours per day as possible. Fitbit data will be wirelessly uploaded to the user’s personal Fitbit account and downloaded by our research team through Fitabase (Small Steps Labs), a web-based database program that collects physical activity and heart rate from the Fitbit cloud. Fitabase allows each participant’s Fitbit data to be batch downloaded at the 1-min level. Fitbit uses a proprietary algorithm to classify each minute as sedentary, light, moderate, or vigorous activity. Nonwear time will be determined based on the lack of heart rate or activity (steps or intensity) at any given minute [62]. Daily adherence to wearing the Fitbit will be defined as >5 min of wear [62]. A 5 min threshold for a valid Fitbit wear day will be used to avoid recording days where the Fitbit had simply been picked up and moved from one place to another, while simultaneously avoiding excluding days where the participant had purposefully worn the Fitbit. Fitbit data will not be used to measure changes in physical activity as participants cannot be blinded to the data collected.

#### Quality of Life

##### Body Image

Body image will be measured using the Body Image Scale (BIS), a 10-item scale developed for cancer survivors that measures perceptions of body disturbance related to cancer and its treatment [63]. Each item is rated on a 4-point Likert scale ranging from 1 (not at all) to 4 (very much). Higher scores indicate poorer body image. The BIS has shown high reliability (Cronbach α=.93), good clinical validity, and sensitivity to changes in psychosocial and physical activity interventions in older breast cancer survivors [63,64].

##### Sexual Function

Sexual function will be assessed using the Female Sexual Function Index (FSFI). The FSFI comprises 19 items assessing 6 domains of sexual functioning over the past 4 weeks: desire (2 items), arousal (4 items), lubrication (4 items), orgasm (3 items), satisfaction (3 items), and pain (3 items) [65]. The FSFI has been shown to be highly acceptable to breast cancer survivors and has good internal consistency (Cronbach α=.83-.96); test-retest reliability (*r*=0.74-0.86); and convergent, divergent, and discriminant validity [66]. The FSFI has been responsive to change in exercise intervention trials [67,68].

##### Fatigue

Fatigue will be assessed through the Patient-Reported Outcomes Measurement Information System Cancer Fatigue v1.0 measure [69]. The computer adaptive testing form will be used; participants will only complete 4-10 items out of the entire question bank. Higher scores indicate higher levels of fatigue. This instrument has shown responsiveness to change over time in prospective [69,70] and intervention [71] studies in cancer survivors.

### Process Evaluation of Peer Mentor Adaptations and Delivery

A multimethod approach will be used to explore the process of intervention delivery and adaptations made by peer mentors. These data will help us describe and understand barriers and facilitators to delivery, identify delivery strategies for use in a future study, and refine how to use delivery methods being tested in this study to maximize the potential for success in future studies. Data collection will occur during and after intervention delivery, and data from all sources will be used iteratively to improve intervention delivery by peer mentors. The data sources for this evaluation will include the following:

Peer mentor session feedback: After each mentoring session, peer mentors will electronically record their confidence and preparedness for delivering the session in REDCap. Questions were developed in partnership with a peer mentor and have been pilot tested and refined with the other peer mentors during mock training sessions. Questions will ask about the extent to which peer mentors used motivational interviewing skills during their session; the helpfulness of the motivational interviewing training in preparing them for the session; their confidence during the session; and general notes and reflections about the session, including any explicit adaptations made.Zoom peer mentoring sessions will be recorded by peer mentors and uploaded to the UC San Diego server. As described above, a random 50% of initial goal-setting sessions and a random 20% sample of the follow-up sessions will be reviewed by [name] to support peer mentor supervision and safety and appropriateness of exercise goals set. A template will be used to guide the exploration of adaptations from the protocol, barriers and facilitators to intervention delivery, and other aspects of the intervention process.[name] will write monthly reflections to document adaptations and process outcomes. Templated reflections will be based on discussions and interactions with multiple stakeholders (peer mentors, research team, and any informal feedback from participants). The reflections will help document key activities, events, and changes occurring over the course of the study.

### Statistical Analysis

#### Feasibility and Acceptability

We will explore how adherence varies between the 3 measures (completion of intervention sessions, wearing the Fitbit, and posting in the Fitbit Community) using descriptive statistics.

##### Postintervention and Follow-Up Quantitative Satisfaction Questionnaires

Descriptive statistics will be used to analyze the questionnaire responses. Responses will be reported as percentages or as mean (SD) as applicable. Open-ended responses will be coded using a standardized process. All open-ended questions and responses will be reviewed by 2 team members. Each response will be assigned at least one code, and codes will be nested into categories. Multiple coders and team consensus will be used to enhance the validity of the coding process and ensure that responses are accurately sorted into representative codes and categories.

##### Postintervention and Follow-Up Qualitative Interviews

Individual interviews will be video recorded and transcribed. A rapid assessment approach will be used to analyze qualitative interviews. The rapid assessment process is defined as “intensive, team-based, qualitative inquiry using triangulation, iterative data analysis, and additional data collection to quickly develop a *preliminary understanding* of a situation from the insider’s perspective” [72]. This method will allow us to feed data from participants back into the ongoing study to improve it. Data that could be fed back may include ways in which peer mentors could be more effective, tools that could be added to the toolbox, and barriers and facilitators that can be feasibly addressed to improve the intervention for other participants. In addition, the project timeline is relatively condensed, so a rapid approach, whereby qualitative analyses are conducted over the course of the intervention, may be more feasible than conducting all qualitative analyses after data collection has ended. Although traditional, in-depth qualitative analyses may be more constructivist, exploratory, and inductive, rapid analysis takes a more positivist approach that is explanatory and deductively oriented [73]. Coding will occur on a monthly basis. A team-based approach will be used to maximize the dependability and validity of the analyses and preliminary findings. As this is a minimally interpretive approach, individuals with limited qualitative training can participate [73]. The project will employ the five rapid analysis steps outlined by [name] [73].

#### Preliminary Intervention Impacts on Physical Activity and Quality of Life

Descriptive statistics (mean [SD] and n [%] where applicable) will be calculated for each variable of interest at T0, T1, and T2. Separate paired *t* tests will assess changes in each variable of interest from T0 to T1 and T1 to T2. The level of significance will be set at α=.05. From the means and SDs, Cohen *d* will be calculated to determine the effect size. These data will allow us to estimate the sample size needed to detect clinically significant intervention effects at an α of .05 and power of 0.80, should the program be tested in a larger efficacy trial.

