### Study Objectives

This study will conduct a single-arm, pre-post pilot trial of Pink Body Spirit, a 3-month remotely delivered, peer-led physical activity intervention, in 30 younger breast cancer survivors. This community-academic partnership project has 3 aims: (1) explore the feasibility and acceptability of the pilot study methods using a parallel mixed methods approach (postintervention quantitative surveys and qualitative interviews), (2) assess the preliminary impact of the intervention on physical activity and quality of life, and (3) use a multimethod approach to explore the process of intervention delivery and adaptations by peer mentors. The overall goal is to develop an intervention that can be disseminated and used by Haus of Volta. This protocol paper reports on the rationale, methodology, and outcome measures of this ongoing community-academic partnership project.

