## Methods

### Study Design and Overview

Thirty younger breast cancer survivors (diagnosed when aged under 50 years and currently aged under 55 years, completed active treatment [ie, surgery, chemotherapy, and/or radiation], and self-reporting <60 min of MVPA per week) will be enrolled into a 3-month physical activity program, Pink Body Spirit. The Pink Body Spirit program is based on an intervention that was successful at increasing physical activity in older survivors delivered by a research interventionist in an academic comprehensive cancer center setting [40,47]. The Pink Body Spirit program will use peer mentors, motivational interviewing, and technology (Fitbit and Fitbit Community) to support behavior change. Five younger breast cancer survivors (diagnosed when aged under 50 years and currently aged under 55 years) have been trained as peer mentors to deliver the program to fellow younger survivors. To help address common barriers to exercise among young cancer survivors, the program is fully remote [8,48]. Participants will complete 6 video chat or phone sessions with their peer mentor biweekly and interact with their peer mentor and other participants through a private Fitbit Community at least weekly. To promote accountability, participants will be informed that their peer mentor will be able to see the physical activity data collected by the Fitbit. Between scheduled sessions, peer mentors will use real-time Fitbit data to identify participants in need of additional support to increase their exercise. At baseline (T0), 3 months (postintervention; T1), and 6 months (follow-up; T2), participants will complete quality of life questionnaires, and MVPA will be measured using the ActiGraph accelerometer. At T1 and T2, participants will also complete quantitative satisfaction questionnaires and qualitative interviews. Using a mixed methods approach (see *Mixed Methods Evaluation* section), findings from quantitative questionnaires and qualitative interviews will be triangulated to explore feasibility, acceptability, and satisfaction with the pilot study methods. Feasibility will be assessed through recruitment and retention metrics and adherence to intervention components (completion of intervention sessions, wearing the Fitbit, and posting in the Fitbit Community). A multimethod process evaluation will explore how the intervention was delivered and adaptations needed or made by peer mentors. Participants will be enrolled on a rolling basis, and intervention process data collected throughout the study will be used iteratively to provide feedback to peer mentors and adapt the program to meet the needs of the target population. The UC San Diego Institutional Review Board approved this study. Figure 1 shows the study flow diagram.

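### Change is tested only from T0 to T1 and from T1 to T2, so whether any benefit over baseline remains at 6 months is left to descriptive means

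*Protocol article*

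**What the plan says.** Under Statistical Analysis, the section on preliminary intervention impacts states that separate paired t "tests will assess changes in each variable of interest from T0 to T1 and T1 to T2". The ActiGraph GT3X+ section says independently that the device "will be used to measure changes in minutes of MVPA from T0 to T1 and T1 to T2". Neither place lists T0 to T2, and nor does any other section.

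The data for that contrast will exist. Study Design and Overview states: "At baseline (T0), 3 months (postintervention; T1), and 6 months (follow-up; T2), participants will complete quality of life questionnaires", with accelerometer-measured MVPA at the same three points. The Follow-Up Assessment (T2) section repeats the baseline questionnaires and the 7-day ActiGraph wear.

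Two other statements in the analysis section matter. Descriptive statistics, as mean (SD) or n (%), "will be calculated for each variable of interest at T0, T1, and T2". Cohen *d*, worked out from the means and SDs, "will be calculated to determine the effect size", with no interval named. The results are then meant to help "estimate the sample size needed to detect clinically significant intervention effects at an α of .05 and power of 0.80" in a later trial.

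**The concern.** Study Objectives describes a "single-arm, pre-post pilot trial of Pink Body Spirit", and its second aim is the preliminary impact on physical activity and quality of life. With no control arm, baseline is the only reference. A statement about impact at 6 months is therefore a statement about T2 against T0, yet the only test that uses T2 compares it with T1.

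That test answers a different question. If outcomes fall from T1 to T2, it does not say whether participants are still better off than at baseline. If it is nonsignificant, it does not show that the gain was held, because a sample of this size can easily miss a partial loss. A participant with T0 and T2 data but no T1 data enters neither planned test.

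At stake is the informativeness of the 6-month data. If the larger trial considered under Future Directions were to use a 6-month endpoint, this pilot as planned would not supply the SD of the within-person change needed to size it.

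**Working it through.** The article gives no power calculation for its own 30 participants. Its α of .05 with power 0.80 refers to a future trial, so there is no stated figure to reproduce. The checks below are illustrations.

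**Inputs from the article.** 30 participants in a single arm; paired t tests; "The level of significance will be set at α=.05". Sidedness is not stated, so two-sided is assumed.

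**Assumed inputs.** SD of 1 at every visit; the same within-person correlation r between any two visits; a T0-T1 gain of 0.5 SD; 24 completers as an alternative to 30.

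**1. How often the T1-T2 test misses a loss.** The SD of a paired change is √(2(1−r)). The standardised change is dz = loss/√(2(1−r)), and power comes from the noncentral t distribution with n−1 degrees of freedom and noncentrality dz·√n.

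At r = 0.6 the SD of the change is √0.8 = 0.894. Losing half the gain gives dz = 0.25/0.894 = 0.28. Losing all of it gives dz = 0.5/0.894 = 0.559.

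| Probability that T1-T2 is nonsignificant | n = 30 | n = 24 |
|---|---|---|
| Half the gain lost, r = 0.6 | 68% | 74% |
| All the gain lost, r = 0.6 | 16% | 25% |

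At n = 30, with r running from 0.4 to 0.8, the half-loss figure falls from 77% to 45% and the full-loss figure from 32% to 1%. A partial loss is missed often across the whole range. A complete loss is missed often only when the correlation is low.

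**2. What the two planned tests would show together.** Take n = 30 and r = 0.5, so the SD of each change is √(2 × 0.5) = 1 and its standard error is 1/√30 = 0.183. Let the mean changes be +0.50 and then −0.25.

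- T0-T1: t = 0.50/0.183 = 2.74, p = 0.010.
- T1-T2: t = −0.25/0.183 = −1.37, p = 0.18.
- T0-T2 (not planned): 0.50 − 0.25 = +0.25, 95% CI −0.12 to 0.62, p = 0.18.

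The planned pair shows a gain and no significant loss. The direct contrast shows that benefit over baseline at 6 months has not been established. For r from 0.3 to 0.7, the T0-T1 p value runs from 0.028 to 0.001 and the T0-T2 p value from 0.26 to 0.088.

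**3. Whether the missing contrast can be rebuilt.** In the same participants, mean(T2−T0) = mean(T1−T0) + mean(T2−T1), so the point estimate can be recovered. The variance cannot: Var(T2−T0) = Var(T1−T0) + Var(T2−T1) + 2Cov, and neither planned test reports the covariance of the two changes. If each interval change has SD 1 and the changes correlate at c, the SD of the T0-T2 change is √(2+2c). For c from −0.8 to +0.3 that is 0.63 to 1.61. For the same net change of +0.25 with 30 pairs, p runs from 0.039 to 0.40.

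**4. What adding the contrast gives.** With 30 pairs, a paired T0-T2 test has 80% power at dz of about 0.53, and with 24 pairs at about 0.60. The 95% CI half-width at n = 30 is 2.045/√30 = 0.37 SDs of the change.

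**The case against.** Several points on the other side stand.

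- A reader might infer that the trial never estimates the 6-month difference from baseline. It does, descriptively: means and SDs are planned at T0 and T2, so a point difference can be read off (exactly in the same completers, approximately otherwise). Cohen *d* names no interval, so a T0-T2 effect size is not excluded either.
- A reader might infer that the investigators will report a nonsignificant T1-T2 test as maintenance. No section says so; that is a risk in interpretation, not a stated plan.
- The section on months 4 to 6 puts the focus on continued engagement with mentors and the program. Scheduled sessions stop at T1, so T1-T2 answers a legitimate question about what happens afterwards.
- The percentages in step 1 describe the low power of T1-T2, not the price of omitting T0-T2. With equal correlations, half of a 0.5 SD gain lost leaves a T0-T2 change of 0.25 SD, and a test of it would be nonsignificant just as often. The benefit of the extra contrast is a direct estimate with its interval, not greater power.
- This is a pilot with feasibility as its first aim, and without a control arm even a clear T0-T2 change would not isolate an intervention effect.

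It can also be argued that a condensed article may leave secondary contrasts to an analysis plan. That carries less weight here, because the article lists its change contrasts explicitly in two places and both lists stop at the same two intervals.

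**Conclusion.** The point holds as a limited one. Followed as written, the plan yields no paired change from baseline to 6 months and no interval for it, although both measurements are collected. Persistence of benefit over baseline is therefore only descriptive, and its precision cannot be recovered from the two planned tests.

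The omission itself rests on the text alone. The size of the T1-T2 problem rests on assumptions: a 0.5 SD gain, equal SDs, equal correlations and two-sided testing. Under these, losing half the gain goes undetected in roughly half to three quarters of trials with 30 pairs. The documents support neither a claim that the 6-month comparison is absent altogether nor one that it undermines the study: no decision rule depends on a T0-T2 test, and the end-of-intervention contrast, T0-T1, is planned. Severity is minor to moderate.

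**What to change.** In the analysis section on preliminary impacts, and in the ActiGraph section for MVPA, add the paired T0-T2 mean change with 95% CI and effect size for each outcome, using every participant with T0 and T2 data whether or not T1 is available. State which interval each Cohen *d* refers to. Report T1-T2 with its 95% CI and describe it as the change after scheduled mentoring ends. A single repeated-measures model with T1-T0 and T2-T0 contrasts would be an acceptable alternative for the baseline comparisons.

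The cost is one or two sentences of analysis wording. No new data, visits or participants are needed.
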